### Measurements

Individuals will receive the following instructions 24 h prior to measuring their biological signals: maintain their normal drug-use routine and sleep and meal hours; do not drink alcohol, tea, coffee, soda, or any food/drink containing caffeine. In addition, on the experiment day they will be asked to ingest a light meal 2 h before initiating the protocol. Patients will be asked to record their activities 24 h following the experiment, such as working hours, sleep schedule, meals, use of medication and any complications that they consider important (e.g., stressful situations). The same instructions will be given in the revaluation after the follow-up period.

In each short-term experimental session and follow-up phase, the biological BP signal, electrocardiogram (ECG) and blood flow will be continuously measured using 500-Hz frequency per channel in WINDAQ software (DATAQ Instruments DI-720 Acquisition, Akron, OH, USA). BP will be recorded by ABPM (Dynamapa Cardios®, São Paulo, Brazil) measured in the nondominant arm by a Dixtal® oscillometric semiautomatic monitor (Dixtal®, DX 2020, Manaus, Brazil) and by Finometer oscillometric equipment (Ohmeda 2300 Monitoring Systems, Englewood, CO, USA). BP values will be obtained immediately before exercise, 30 and 60 min after each intervention (ABPM, Dixtal® and Finometer methods), and 24 h (ABPM) after the end of the intervention. ECG will be evaluated in the DII derivation (right and left arm). Forearm blood flow will be collected by venous occlusion plethysmography [42] apud [43] (Hokanson®/EC6 plethysmograph, Bellevue, WA, USA). During blood flow signal collection, BP values will be registered by Dixtal® oscillometric semiautomatic monitor (Dixtal®, DX 2020, Manaus, Brazil). All the measurement methods will be repeated in an experimental session without any intervention after the follow-up period in the same sequence and procedure.

## Outcomes

### Primary outcome

#### Blood pressure

For the BP measurement in the office, analysis will consider the difference between post-intervention and pre-intervention values. For ambulatory analysis, BP will be considered as sleep and awake periods, and the difference between 24-h post-intervention and pre-intervention values. In the follow-up analysis, baseline BP values (considering control session values without intervention) and post-training BP values will be evaluated.

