### Random allocation sequence

Randomization will be done using a sealed opaque envelope. All the patients will be submitted to perform four short-term interventions (within design): mild aerobic exercise, moderate aerobic exercise and high-intensity aerobic exercise and a control session, in random order and on separate days. After the short-term sessions, all the patients will be randomly allocated into four groups and followed up for 8 weeks (between design): mild aerobic exercise group, moderate aerobic exercise group, high-intensity aerobic exercise group and the control group.

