## Statistical analysis

### Power and sample size

Sample size was calculated using ABPM as the main outcome. Considering the high variance in the results with resistant hypertensive patients [29, 30] and the meta-analysis results of Fagard [28] with hypertensive patients, BP reduction after endurance training of 7 mmHg from SBP and 5 mmHg from DBP was used in the calculation. In order, to provide 80% power to detect a difference of 3 mmHg between the four distinct conditions (exercise intensity and control), a total of 32 patients are indicated to give sufficient power for the study (*n* = 8 for each group). Considering the possible sample loss, 12 patients will be included in each group.

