### Analysis plan

Intragroup and intergroup differences between dependent variables (BP, autonomic modulation, baroreflex sensitivity, blood flow and vascular resistance) considering pre and post interventions (short-term), baseline and post intervention (dependent factor), and exercise intensities or control (independent factor) will be analyzed by two-way analysis of variance (ANOVA) for repeated measures with the Bonferroni post hoc test. Multiple linear regression will be used for analyzing confounding factors (dietary habits and unsupervised physical exercise practice in the follow-up period). Pearson’s correlation test will be used for analyzing the relation between short-term and long-term results. Intention-to-treat will be considered for the patients with an incomplete follow-up period. A *p* value < 0.05 will be considered significant for all evaluations.

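### In the short-term crossover, scoring BP as post minus pre fixes the coefficient on the session's pre reading at 1; estimating it would be at least as precise at almost no cost

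*Protocol article*

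**What the plan says.** All from the Protocol article.

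- Random allocation sequence: "All the patients will be submitted to perform four short-term interventions (within design"; the sessions take place "in random order and on separate days". The short-term phase is therefore a four-session crossover.
- Measurements: "BP values will be obtained immediately before exercise, 30 and 60 min after each intervention". The pre and post readings belong to the same session.
- Outcomes, Blood pressure: "For the BP measurement in the office, analysis will consider the difference between post-intervention and pre-intervention values".
- Analysis plan: differences within and between groups, for BP and for the autonomic and blood-flow variables, "will be analyzed by two-way analysis of variance (ANOVA) for repeated measures with the Bonferroni post hoc test". The only covariate adjustment named concerns other factors in another phase: "Multiple linear regression will be used for analyzing confounding factors (dietary habits and unsupervised physical exercise practice in the follow-up period". The pre-session reading is not among them.

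**The concern.** In a parallel-group trial, subtracting baseline serves mainly to remove differences between patients. In this phase those differences are already gone, because each patient supplies all four conditions. What the pre reading can still tell us is how that patient stood on that day.

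Subtraction uses this information with a coefficient fixed at 1. That is the best weight only if the pre reading predicts the post reading one for one. Any short-term fluctuation in the pre reading weakens that relation. The fixed coefficient then over-corrects and passes the fluctuation into each exercise-versus-control and intensity-versus-intensity contrast.

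At stake is the width of those intervals. The acute effect is part of the primary outcome (Abstract) and the subject of the first research question, and the readings needed to narrow the intervals are already collected.

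**Working it through.** **Inputs.** From the article: four sessions per patient in random order; 48 patients (Abstract), all taken as analysed; pre and post readings in one session; significance level 0.05, with sidedness not stated and two-sided assumed. Not in the article, so assumed: the within-patient SD of a reading, s; the within-patient, same-session pre/post correlation, r; and equal pre and post variances.

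**The plan's own figure.** Power and sample size gives 32 patients (8 per group), raised to 12 per group for loss, "to provide 80% power to detect a difference of 3 mmHg between the four distinct conditions (exercise intensity and control". With 8 per group, two-sided 5% and a normal approximation, the implied SD is 3 / (2.802 × √(2/8)) = 3 / 1.401 = 2.14 mmHg. No SD is stated, so 32 is neither confirmed nor refuted. It was set for ambulatory BP, with the number given per group, and supplies no variance for the office crossover comparison.

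**Step 1: the ANOVA compares changes.** For condition E against control C at a given post time, the condition-by-time contrast is (post_E − pre_E) − (post_C − pre_C), which is the difference of two change scores.

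**Step 2: variance of one patient's contrast between two conditions, patient effect removed.**
- Post values only: 2s²
- Change score: 4s²(1 − r)
- Adjusted for the pre reading: 2s²(1 − r²)

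Adjusted/change = (1 − r²) / [2(1 − r)] = (1 + r)/2, which is below 1 for every r < 1.

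**Step 3: which noise is added.** Write s² = d² + e², where d is the SD of a day effect shared by the session's readings and e the SD of reading noise. Then r = d²/(d² + e²) and s²(1 − r) = e², so the change-score variance is 4e². The day effect has dropped out; half of what remains (2e²) comes from the two pre readings. Simulation (48 patients, 4 sessions, 3000 runs) agrees. SEs in mmHg:

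| d | e | r | post only | change | adjusted |
|---|---|---|---|---|---|
| 0 | 5 | 0 | 1.02 | 1.42 | 1.03 |
| 5 | 5 | 0.50 | 1.44 | 1.45 | 1.26 |
| 7 | 5 | 0.66 | 1.72 | 1.44 | 1.30 |
| 8 | 4 | 0.80 | 1.85 | 1.14 | 1.09 |

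**Step 4: size over a range of r.** If the adjusted analysis has 80% power, the change score has Φ(2.802 × √((1 + r)/2) − 1.960). The patients it needs to match 48 analysed with adjustment are 48 × 2/(1 + r).

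| r | adjusted/change variance | power of change score | patients to match 48 |
|---|---|---|---|
| 0.3 | 0.65 | 61.7% | 74 |
| 0.5 | 0.75 | 67.9% | 64 |
| 0.7 | 0.85 | 73.3% | 57 |
| 0.8 | 0.90 | 75.7% | 54 |
| 0.9 | 0.95 | 78.0% | 51 |

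Example with assumed s = 6 mmHg and r = 0.5: SE = √(4 × 36 × 0.5/48) = √(72/48) = 1.22 for change and √(2 × 36 × 0.75/48) = √(54/48) = 1.06 adjusted.

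**Step 5: the outcome can stay.** Let post = patient + condition + position + b × (pre − patient's mean pre). Subtract pre from both sides: the slope becomes b − 1, the patient term absorbs the patient's mean, and the condition terms are unchanged. Change score and post value therefore give the same condition effects once the pre reading is in the model.

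**Step 6: cost in degrees of freedom.** At one post time, 48 × 4 = 192 values. Residual df = 192 − 1 − 47 (patients) − 3 (conditions) − 3 (positions) = 138 without the slope and 137 with it.

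**The case against.** The strongest case against is that the plan makes no error here. Session order is random, so the change score is unbiased; in simulation with assumed variances, type I error at the 5% level stayed at about 4% to 5.5% for both methods. The within-session fall is itself a target: the Background hypothesises that each intensity lowers BP after exercise, and the Analysis plan includes intragroup differences. Readings taken within one session may be highly correlated, and at r = 0.8 to 0.9 the loss is only about 2 to 4 power points. All of this stands. It limits the point to efficiency and means that the intragroup test must be kept.

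It could also be said that covariates are left to an analysis plan not shown here. That does not dispose of the point: the article states the score and the model, and the comment concerns that stated method.

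A reader might infer more than the article supports:
- That subtraction adds day-to-day noise. It does not. Raising the day SD from 0 to 7 mmHg left the change-score SE at 1.42 to 1.44, while the post-only SE rose from 1.02 to 1.72.
- That the change score is worse than ignoring the pre reading. This needs r < 0.5, and nothing in the article fixes r.
- That the stated sample size fails for this reason. It was set for ambulatory BP, not for this comparison.

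**Conclusion.** The point holds as one of efficiency. For between-condition comparisons in the short-term phase, the stated score and ANOVA are never more precise than adjustment for the same-session pre reading, apart from one degree of freedom. They are less precise whenever r < 1. The change-score variance exceeds the adjusted variance by a factor of 2/(1 + r): 1.54 at r = 0.3, 1.33 at 0.5, 1.18 at 0.7 and 1.05 at 0.9.

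The size cannot be settled from the article. It rests on an assumed r, equal pre and post variances, a slope common to all conditions and, for the patient counts, all 48 patients analysed. No calculation was made for the autonomic and blood-flow variables; the same algebra applies, with their own r. There is no case for calling the planned analysis biased or invalid.

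**What to change.** In the Analysis plan, for between-condition comparisons in the short-term phase, specify a model with patient, condition and session position, and the same-session pre reading as a covariate, entered as its deviation from the patient's mean over the four pre-session readings. Apply it to the 30- and 60-minute values. The same model can serve the autonomic and blood-flow variables measured before and after each session.

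Leave the post-minus-pre definition under Outcomes as it is, and keep the planned within-condition pre/post test of post-exercise hypotension alongside the model.

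The cost is one sentence, one degree of freedom and the assumption of a common slope across conditions. No new data or visits are needed. The article reports that recruitment is still open, so the change can be recorded before analysis.

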**Methods/design:**

This is a randomized controlled clinical trial. Forty-eight patients with resistant hypertension will be submitted to perform four short-term interventions: aerobic exercise sessions (mild-, moderate- and high-intensity) and control session, in random order and on separate days. After the short-term sessions, the patients will be randomly allocated into four groups for 8 weeks of follow-up: mild-, moderate- and high-intensity aerobic exercise, and a control group. The primary outcome is the occurrence of blood pressure reduction (office and ambulatory analysis, and acute and chronic effects). Secondary outcomes are autonomic and hemodynamic mechanisms: cardiac and vasomotor autonomic modulation, spontaneous baroreflex sensitivity, forearm blood flow and vascular resistance.

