### Eligible participant and exclusion criteria

Patients with resistant hypertension, who are aged between 40 and 70 years, will be recruited from the Lauro Wanderley University Hospital at the Federal University of Paraiba, Brazil, being men or women (women must be postmenopausal, nonmenstruating for at least 1 year and not using hormone replacement therapy), with Body Mass Index ˂40 kg/m^2^ and able to do physical exercise. Patients with resistant hypertension when BP levels are ≥140/90 mmHg for SBP/DBP, respectively, using three or more antihypertensive agents in appropriate doses and combinations, or with controlled BP using four or more antihypertensive agents, will be considered [3] in addition to considering ambulatory BP monitoring (ABPM) records. Controlled BP will be considered for SBP and DBP: at 24 h <130 mmHg and <80 mmHg; awake <135 mmHg and <85 mmHg; and sleeping <120 mmHg and <70 mmHg [40].

After clinical assessment and verifying medical records and biochemical data, patients can be excluded for having a history of ischemic stroke, coronary heart disease, chronic obstructive or restrictive pulmonary disease, peripheral arterial disease, hypo/hypernatremia, hyper/hypothyroidism, chronic atrial fibrillation or a change in drug therapy for an experimental protocol. In the follow-up phase, patients who do not participate in 90% of the exercise training sessions, miss three consecutive training sessions or present any osteoarticular disease that prevents them from continuing the physical training program will be considered as sample loss.

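### The acute 24-h ambulatory outcome is measured against a reading taken just before the session, so a within-session test can show a fall in blood pressure without any exercise effect.

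*Protocol article*

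**What the plan says.** The Abstract states: "The primary outcome is the occurrence of blood pressure reduction (office and ambulatory analysis, and acute and chronic effects"). Under Outcomes, Blood pressure, the acute ambulatory component is defined: "For ambulatory analysis, BP will be considered as sleep and awake periods, and the difference between 24-h post-intervention and pre-intervention values".

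The timing is given under Measurements: "BP values will be obtained immediately before exercise, 30 and 60 min after each intervention", with ABPM listed among the methods used at those time points, "and 24 h (ABPM) after the end of the intervention". That section describes no 24-h recording before an acute session.

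The Analysis plan tests "Intragroup and intergroup differences between dependent variables" by two-way repeated-measures ANOVA with Bonferroni post hoc comparisons, so each condition's own pre/post change is tested as well as the contrast between conditions.

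The training phase is handled differently: "In the follow-up analysis, baseline BP values (considering control session values without intervention) and post-training BP values will be evaluated". There the baseline comes from a session with its own post-session ABPM, so like can be compared with like.

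**The concern.** The outcome definition and the measurement schedule do not fit together. A 24-h mean includes the night, whereas a reading just before the session does not. The difference between them therefore contains the ordinary day-to-night fall as well as any effect of exercise, and it does so after seated rest too.

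This bears on the stated aims. The primary outcome is worded as whether blood pressure falls, the Research question asks whether it is reduced after each intensity, and a within-condition test is planned. A significant 24-h reduction after each exercise session could be reported as post-exercise hypotension when it is only the night.

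**Working it through.** The article gives no figure for this offset, so there is none to reproduce. The calculation under Power and sample size is built on reductions after endurance training and on group sizes in the training phase, and it is not used here.

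**Inputs**
- Thresholds for controlled blood pressure (Eligible participant and exclusion criteria): 24 h 130/80 mmHg and "awake <135 mmHg and <85 mmHg; and sleeping <120 mmHg and <70 mmHg". These are cut-offs, not patient means, and serve only as a proxy for the spread between day and night.
- 48 patients, each attending all four sessions (Abstract; Random allocation sequence).
- Significance level 0.05 (Analysis plan), taken as two-sided.
- Assumption: the pre-session reading lies at awake level, 135/85.
- Assumption: the SD of the 24-h-minus-pre change, which is not stated, lies between 7 and 20 mmHg.

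**Step 1: are the thresholds coherent as a proxy?** With 16 h awake and 8 h asleep:
- SBP: (135×16 + 120×8)/24 = 130
- DBP: (85×16 + 70×8)/24 = 80

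Both equal the 24-h thresholds.

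**Step 2: expected change with no exercise effect.** 24-h level minus awake level:
- SBP: 130 − 135 = −5 mmHg
- DBP: 80 − 85 = −5 mmHg

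For scale, the Background puts acute post-exercise reductions at 2 to 12 mmHg.

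**Step 3: how often would a within-session test declare a reduction?** This is a paired t-test with 47 degrees of freedom, critical value 2.012 and noncentrality −5/(SD/√48). The result is the lower-tail rejection probability. Without an offset it would be 2.5%.

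| SD of change (mmHg) | SD/√48 | Noncentrality | Declares a reduction |
|---|---|---|---|
| 7 | 1.010 | −4.95 | 99.8% |
| 10 | 1.443 | −3.46 | 92% |
| 15 | 2.165 | −2.31 | 62% |
| 20 | 2.887 | −1.73 | 40% |

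These figures are for an unadjusted test. If Bonferroni is applied over the four within-session comparisons (level 0.05/4 = 0.0125, critical value 2.597), the same formula gives 99%, 80%, 40% and 21%. The number of comparisons is my assumption.

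**Step 4: exercise versus control.** If both sessions carry the same offset, the expected contrast is −5 − (−5) = 0. In 4,000 simulated trials with 48 patients, the paired exercise-minus-control test rejected in 4.6% (SD 7), 4.6% (SD 10) and 5.2% (SD 15), close to the nominal 5%.

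**Step 5: does subtracting the pre-session reading cost power?** The variance of the exercise-minus-control contrast is 2(a² + b² − 2rab) with the pre reading subtracted and 2a² without. Here a is the within-patient SD of the 24-h mean, b that of the pre reading and r their correlation, none of which is stated. For illustration, take a = 5, a difference of 3 mmHg and n = 48:
- Not subtracted: variance 50, power 82%.
- b = 8, r = 0.3: 2(25 + 64 − 24) = 130, power 43%.
- b = 5, r = 0.3: 2(25 + 25 − 15) = 70, power 68%.
- b = 5, r = 0.5: 2(25 + 25 − 25) = 50, power 82%.
- b = 5, r = 0.7: 2(25 + 25 − 35) = 30, power 96%.

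The effect on power can be a loss, none or a gain.

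**The case against.** **The comparator may be another recording.** ABPM is used at eligibility, with separate 24-h, awake and sleep criteria, and the schedule figure is not shown. The article does not exclude a matched 24-h baseline, so nobody can say that none exists. That stands. But the eligibility ABPM is never named as the pre-intervention value, and the only pre-intervention reading described for a session is the one just before it.

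**The control session already deals with it.** Every patient has a seated control session and conditions are compared with each other, so the mean offset drops out of that contrast. This stands, provided that sessions start at similar times of day. It does not protect the intragroup test, which is also planned.

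**The 5 mmHg is not data.** Correct. The thresholds are not means, and an awake average includes ordinary activity. A quiet resting reading could lie below it, and the offset would then be smaller or reversed.

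**Stronger readings that the article does not support.** A reader might infer that the pre-session reading is also subtracted from the sleep and awake averages, which on the same proxy would give 120 − 135 = −15 mmHg for sleep. The article states the subtraction for 24 h only and says merely that sleep and awake periods are considered. For awake the proxy offset would in any case be 135 − 135 = 0. A reader might also infer that the exercise-versus-control comparison is biased, that power is necessarily lost, or that the sample size is undermined. Steps 4 and 5 do not bear out the first two, and the sample size concerns the training phase.

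**Conclusion.** The concern holds in a limited form. As written, the acute 24-h outcome has no like-for-like pre-intervention value, and the planned within-condition test can report a reduction after any session, seated rest included. The size, about −5/−5 mmHg and a false declaration rate of roughly 40% to 99.8% for SDs from 20 down to 7 mmHg, depends on three things: the thresholds as a proxy, a pre reading at awake level, and an unadjusted test in 48 patients.

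The defect is confined to within-session inference on acute 24-h ABPM. The 8-week analysis, with control-session values as baseline, is untouched. It is more than missing detail, because the outcome formula and the measurement times are both stated and do not match.

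**What to change.** Define the acute ambulatory outcome as exercise-session ABPM minus control-session ABPM in the same patient over the same window, separately for 24 h, awake and sleep. Use the pre-session reading at most as a covariate. State in the Analysis plan that no conclusion on acute ambulatory blood pressure rests on the within-session pre/post test. If the sponsor did intend a matched 24-h baseline, name that recording and when it is made.

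The cost is one reworded outcome definition and one line in the analysis plan, settled before analysis. The control-session recordings are already planned for every patient, so no new recordings are needed.

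### The 8-week blood pressure comparison is planned as a raw change-score test from one control-session baseline; this is valid, but baseline-adjusted ANCOVA on data already collected would usually be more precise.

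*Protocol article*

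**What the plan says.** Under Primary outcome, Blood pressure, the article defines the follow-up comparison: "In the follow-up analysis, baseline BP values (considering control session values without intervention) and post-training BP values will be evaluated". The 8-week baseline is therefore one of the four short-term sessions, the resting control session.

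The Analysis plan names the test. Differences within and between groups "will be analyzed by two-way analysis of variance (ANOVA) for repeated measures with the Bonferroni post hoc test", with baseline versus post-intervention as the repeated factor and exercise intensity or control as the group factor. The only covariates it names are in a separate regression: "Multiple linear regression will be used for analyzing confounding factors (dietary habits and unsupervised physical exercise practice in the follow-up period"). Baseline BP is not among them.

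More BP data than the control session exist before training. Under Random allocation sequence, "All the patients will be submitted to perform four short-term interventions (within design"), in random order on separate days, and allocation to the 8-week groups comes afterwards. Under Measurements, "BP values will be obtained immediately before exercise" at each session, with further readings at 30 and 60 min and by ambulatory monitoring (ABPM) over 24 h. The post-training assessment is one session without intervention, run by the same procedure.

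**The concern.** A change score fixes the slope of the post-training value on baseline at 1. All day-to-day error in the one baseline session then passes into the change. ANCOVA estimates the slope from the data, so it gives less weight to a noisy baseline and removes the part of any chance baseline imbalance that reflects regression to the mean.

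For office BP, three further pre-session readings per patient are taken before the second randomisation but have no role in the 8-week comparison.

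This matters because the comparison is small: 12 patients per group are planned and 8 are assumed to be enough. What is at stake is the width of the intervals and the power, not the validity of the test.

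**Working it through.** **The plan's own figure.** Power and sample size gives 8 per group for 80% power to detect 3 mmHg, based on ABPM. No SD or correlation is stated, so the figure cannot be reproduced; only the implied SD can be found. From n = 2(1.96 + 0.84)² SD² / 3² with n = 8, the SD of change is about 2.1 mmHg. The ratios below do not depend on it.

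**Inputs.** From the article: two time points, four groups, 8 per group (12 recruited), and four sessions before the second randomisation. Assumed: correlation rho between single visits, since none is given, and equal variance at all visits.

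**Step 1. What the planned test is.** With two time points, the group-by-time F test equals a one-way ANOVA of (post − baseline).

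**Step 2. Variance of a group contrast, in units of the single-visit variance.**
- Change score: 2(1 − rho)
- ANCOVA on one baseline: 1 − rho², so the ratio to change score is (1 + rho)/2
- ANCOVA on the mean of four equally correlated baselines: 1 − 4rho²/(1 + 3rho)
- Small-sample cost of one covariate: factor 1 + 1/(df − 2). With df = 28 at 8 per group this is 1 + 1/26 = 1.038; with df = 44 at 12 per group it is 1 + 1/42 = 1.024.

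| rho | Change | ANCOVA, one baseline | Ratio | Ratio with cost, 8 per group | ANCOVA, mean of four | Ratio | Ratio with cost, 8 per group |
|---|---|---|---|---|---|---|---|
| 0.4 | 1.20 | 0.84 | 0.70 | 0.727 | 0.709 | 0.591 | 0.614 |
| 0.6 | 0.80 | 0.64 | 0.80 | 0.831 | 0.486 | 0.607 | 0.630 |
| 0.7 | 0.60 | 0.51 | 0.85 | 0.883 | 0.368 | 0.613 | 0.636 |
| 0.8 | 0.40 | 0.36 | 0.90 | 0.935 | 0.247 | 0.618 | 0.641 |
| 0.9 | 0.20 | 0.19 | 0.95 | 0.987 | 0.124 | 0.622 | 0.646 |

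At rho 0.95 the one-baseline ratio with the cost is 1.012 at 8 per group, so ANCOVA is then very slightly worse.

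**Step 3. Which column applies.** For ABPM, only the control session gives a recording free of a preceding exercise bout, so the one-baseline columns apply. The four-reading columns apply to office pre-session BP only.

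**Step 4. Relaxing equal correlation (office BP).** The four sessions precede training and the post-training session follows it, so baselines may correlate more with each other (r_b) than with the post value (r_p). The ANCOVA variance is then 1 − r_p² / ((1 + 3r_b)/4).
- r_b = 0.8, r_p = 0.6: 1 − 0.36/0.85 = 0.576. Divided by the change-score variance of 0.80, the ratio is 0.72 (one baseline: 0.80).
- r_b = 0.9, r_p = 0.8: 1 − 0.64/0.925 = 0.308. Divided by 0.40, the ratio is 0.77 (one baseline: 0.90).

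**Step 5. Power.** Simulation used 20,000 trials per setting, the omnibus F test, three exercise arms at −3 mmHg and 8 per group, calibrated so that the change-score test has 80% power. One-baseline ANCOVA gives about 93%, 90%, 85%, 83% and 80% at rho 0.3, 0.5, 0.7, 0.8 and 0.9. Four-reading ANCOVA gives 94% to 96% throughout, under equal correlation.

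**The case against.** The strongest reply is that nothing here is an error. Repeated-measures ANOVA after randomisation is a standard, unbiased analysis, and covariate adjustment is often left to an analysis plan, which is not shown. The first part stands in full. The second stands only in part, because the article itself names the test, the factors and the baseline.

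The control session also has a good rationale as baseline. It is the like-for-like match to a post-training session without intervention, including the later readings. That stands, and ANCOVA can keep it as the covariate.

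Four stronger readings are tempting, and the document does not support them:
- A reader might infer that the planned analysis is biased. It is not; randomisation protects it, and the loss is in precision only.
- A reader might apply the largest gain (about 39% less variance, a 22% narrower interval, some 60% more patients) to the trial's main outcome. That figure needs four averaged readings and equal correlation at all visits. It does not carry over to ABPM, on which the trial was sized.
- A reader might argue that enrolling both controlled and uncontrolled patients makes the change score worse. The reverse is true: stable differences between patients cancel in a change score, and they raise rho, where one-baseline ANCOVA gains least.
- A reader might call the adjustment free. It uses at least one error degree of freedom, about 4% of variance at 8 per group.

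**Conclusion.** The point holds as a recommendation on efficiency. The plan fixes a change-score comparison where baseline adjustment would usually be more precise, in a phase with 8 to 12 patients per group.

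For ABPM the gain is modest and depends on an unstated correlation: useful at rho 0.4 to 0.7, small at 0.8 (ratio 0.935 after the small-sample cost) and essentially nil from 0.9 upwards.

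For office pre-session BP the gain is more dependable: 38% to 41% less variance under equal correlation (rho 0.4 to 0.8), and 23% to 28% in the two unequal-correlation cases, all before the roughly 4% small-sample cost.

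The existence and direction of the gain are secure except at very high rho with one baseline. The exact size is not, because the article gives neither an SD nor a correlation.

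**What to change.** State in the Analysis plan that 8-week BP is analysed by ANCOVA: post-training BP as the outcome, group as the factor, and control-session BP as the covariate, matched to the same measure and time point. For office pre-session BP, use the mean of the four pre-session readings as the covariate, or add that mean to control-session BP. All these values precede the second randomisation, so adjusting for them introduces no bias.

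Visit position of the control session is best left out or made optional, since as a four-level factor it uses 3 degrees of freedom.

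The cost is a change of wording and one error degree of freedom per covariate. No new measurement is needed.
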